### Strategies to improve adherence to interventions {11c}

All participants will be pulled into a WeChat group and they can ask questions directly. Participants need to clock in one time every week and will be reminded monthly about their rehabilitation plan by phone.

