### Intervention description {11a}

The comparator group receives routine rehabilitation training after surgery, which is the first option for ACLR (Table 1). The intervention group program adds proprioceptive training on the basis of routine rehabilitation training, three times a week, 20 min each time. The intervention will be conducted on the first day after surgery.

**Table 1 Tab1:** The routine rehabilitation training

Focus on functional training
1. Jogging training, 10 min
2. Single-leg squat exercise, three series of 10 repetitions
3. Jump training, three series of 10 repetitions
4. Strength exercise of quadriceps femoris, 70–80% 1RM (1 repetition maximum), two series of 8–12 repetitions

Proprioceptive program: ① The therapist ties the mobile phone with the software to measure the flexion angle of the joint above the patient’s lower leg. Participants take a supine position with eyes closed and the therapist passively flexes the knee joint on the operative side of the participants to any angle. Participants will be asked to repeatedly bend to this angle, three series of 10 repetitions, per angle. Three angles are randomly set(5 degrees of error); ② The therapist ties the mobile phone with the software to measure the flexion angle of the joint above the patient’s lower leg. Participants take a sitting position with eyes closed. Patients actively extend the knee joint to any angle. Participants will be asked to repeatedly bend to this angle, three series of 10 repetitions, per angle. Three angles are randomly set (5 degrees of error).

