### Relevant concomitant care permitted or prohibited during the trial {11d}

In order to make the patients receive the same rehabilitation as possible within 3 months after surgery, the early rehabilitation training is printed and taken home after discharge (Table 2). Participants will be informed that rehabilitation interventions, other than those that will be received during the period of the study, will not be allowed.

**Table 2 Tab2:** The early rehabilitation training

**Stage**	The early rehabilitation training
0–3 weeks	1. Using fascial knife to reduce swelling, 5 min 2. Moving patella, 2 series of 10 repetitions 3. Flexing knee joint (0–90°), three series of 10 repetitions 4. Straightening the knee joint to the level of the healthy side 5. Straight leg raising (SLR), three sets of 10 reps 6. Glute bridge, three sets of 10 reps 7. Walking with crutches
3–6 weeks	Besides the above scheme: 1. Increasing the flexion angle of the knee joint to achieve a full range of activities in 6 weeks 2. Gradually reducing the use of crutches, and do not use braces and crutches when walking for 6 weeks 3. The resistance can be increased when the straight leg is raised 4. Step up exercise 5. Intensive exercise of vastus medialis
6–12 weeks	If the above actions have been completed easily, go to the next step (pay attention to the training intensity in 8–10 weeks, and the ligament strength in the remodeling period is insufficient), and focus on flexibility training: 1. Squat training against the wall 2. Abduction training of muscles around the hip 3. Power bicycle training 4. Stair down training (after 10 weeks) 5. Seat squatting training

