## Assignment of interventions: blinding

### Who will be blinded {17a}

Because the implementers and patients of the proprioceptive training group and the conventional group can clearly observe; Therefore, the blind method of this study is only blind for the evaluators of outcome indicators and data analysts. Data collection and analysis shall be conducted independently by researchers who do not participate in the trial.

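### All participants join a WeChat group with no stated split by arm, so comparator patients may learn of and imitate the trained task, and no step records whether they do

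*Protocol article*

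**What the plan says.** - **Adherence (Protocol article, Strategies to improve adherence to interventions {11c}).** "All participants will be pulled into a WeChat group and they can ask questions directly". Participants also clock in once a week and get a monthly phone reminder. No division of the group by arm and no rule on content is given.
- **Contrast between arms (Intervention description {11a}).** "The intervention group program adds proprioceptive training on the basis of routine rehabilitation training, three times a week, 20 min each time". Nothing else distinguishes the arms.
- **How the training is delivered (same section).** For both exercises, "The therapist ties the mobile phone with the software to measure the flexion angle of the joint above the patient’s lower leg". In the first, "the therapist passively flexes the knee joint on the operative side of the participants to any angle". In the second the patient sits with eyes closed: "Patients actively extend the knee joint to any angle", and then reproduces that angle.
- **Blinding (Who will be blinded {17a}).** "the blind method of this study is only blind for the evaluators of outcome indicators and data analysts".
- **Safeguards.** Under Relevant concomitant care {11d}, "Participants will be informed that rehabilitation interventions, other than those that will be received during the period of the study, will not be allowed". Adverse event reporting and harms {22} lists receipt of another rehabilitation programme midway among the grounds for rejecting a patient.
- **Outcome used for the sample size (Study outcomes {12}; Sample size {14}).** Joint position sense is tested seated: active knee extension to 15, 45 and 75°, then reproduction of the angle with eyes closed. The sample size rests on this measure, with d = 0.97.

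**The concern.** In an unblinded trial of an add-on exercise programme, a channel open to both arms is a route for contamination. Questions that intervention patients ask about their extra exercises concern the whole experimental contrast.

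The second exercise and the joint position sense test are nearly the same task: seated, eyes closed, active extension, reproduce the angle. A comparator patient who copies that exercise at home rehearses the outcome, so even partial, unsupervised copying could narrow the difference between arms.

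Any such dilution biases the comparison towards no effect. The stated safeguards work by instruction and by exclusion. Copying that goes unnoticed dilutes the contrast. Copying that is noticed may lead to rejection of the patient, in a trial that allows for only four losses (40 − 36).

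**Working it through.** **Inputs from the protocol article.** Sample size {14}: d = 0.97, alpha = 0.05 (sidedness not stated), power 80%, 36 evaluable, 10% loss, 40 in total. Trial design {8}: 1:1 allocation.

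**Step 1: reproduce the plan's figure.** For a two-sample t-test with n per arm, the noncentrality is d × √(n/2) on 2n − 2 degrees of freedom.
- Two-sided 0.05, n = 18: 0.97 × √9 = 2.91 on 34 df, power 0.807. With n = 17 power is 0.783, so 18 per arm is the smallest size that reaches 80%. The total is 36, and 36 / 0.9 = 40. Both stated figures reproduce.
- A one-sided test would need 14 per arm (28 in total), so the plan's figure is two-sided.
- If all 40 are retained (n = 20): 0.97 × √10 = 3.07 on 38 df, power 0.848.

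**Step 2: dilute the contrast.** Let c be the share of the between-arm difference that is lost, so that the diluted effect is 0.97 × (1 − c), with the standard deviation held fixed. c is the share of comparator patients who copy, multiplied by the share of the benefit they gain. In an arm of 20, c = 5% means one patient copying with full benefit (1/20) or two copying with half benefit (2/20 × 0.5). The documents give no value for c, so the range below is an assumption.

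| c (assumed) | Diluted d | Power, 18 per arm | Power, 20 per arm | Evaluable N for 80% power | N after 10% loss |
|---|---|---|---|---|---|
| 0 | 0.970 | 0.807 | 0.848 | 36 | 40 |
| 5% | 0.921 | 0.766 | 0.810 | 40 | 45 |
| 10% | 0.873 | 0.721 | 0.767 | 44 | 49 |
| 20% | 0.776 | 0.619 | 0.667 | 56 | 63 |

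**Step 3: read the table.** With the full planned loss, a 5% dilution already takes power below 80%. With no loss, the trial absorbs 5% (0.81) but not 10% (0.77).

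**Step 4: look for a check on exposure.** The sections on adherence, concomitant care, harms, and data collection were compared. None describes how a comparator patient's use of the proprioceptive exercises would be asked about or recorded. The weekly clock-in exists, but no such question is attached to it.

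**The case against.** The case against is substantial on several points.

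- **The shared group is inferred from a singular noun.** The text does not say that training content is posted or that patients discuss exercises with one another; asking questions may mean asking the team. This stands as a limit: exposure is possible, not shown. But the sentence covers all participants and states no split, so the ordinary reading is one group.
- **The training is not simply a phone exercise that can be picked up from a chat.** The phone is an angle sensor that a therapist attaches in both exercises, and the first needs the therapist to position the knee. This stands. Only the second exercise can plausibly be imitated, and without supervision. Full benefit from copying is therefore the extreme case.
- **Safeguards exist.** They reduce the risk but do not remove it, since they depend on patients complying and on copying being detected.
- **Comparator patients may already know that extra training exists**, from the information pamphlet and the discussion before consent. That is likely. Knowing that it exists still differs from ongoing contact with people who are asking how to do it.
- **The power loss is smaller than the 18-per-arm figures suggest.** This is right if fewer than 10% are lost. The planned baseline-adjusted repeated measures analysis may also be more efficient than a t-test, but the documents give no correlation with which to quantify that.

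A reader might also infer that the group unblinds evaluators. No section places an evaluator or analyst in it, and the blinding section assigns data collection and analysis to researchers outside the trial. Nor does the rule in section {20c} on patients wishing to leave the comparator group show that the chat would prompt withdrawals. That rule is a separate problem.

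**Conclusion.** The point holds as a risk. As described, the adherence measure gives both arms of an unblinded trial a common channel, the active exercise resembles the outcome on which the trial is powered, and no exposure check is stated. It would be tempting to say that the shared group does expose comparator patients and does dilute the effect. The documents do not support that, because they report no uptake and give no contamination rate.

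The size is therefore conditional. Under assumed losses of contrast of 5% to 20%, power falls to between 0.77 and 0.62 with 18 per arm, or to between 0.81 and 0.67 if all 40 are retained. These figures assume a two-sided t-test at 0.05, a true d of 0.97 and an unchanged standard deviation. If there is no dilution, the stated 36 and 40 stand. This is a cheap improvement to the design, not an error in its figures.

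**What to change.** In section {11c}:

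1. Replace the shared WeChat group with one group per arm, each moderated by existing unblinded staff.
2. State that no outcome evaluator or data analyst is a member of either group. This is a precaution; nothing in the text says that they would be.
3. Add one question to the existing weekly clock-in, worded the same for both arms, on any knee exercise done outside the assigned programme. Comparator exposure is then on record and can be reported beside the result.

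Cost: one additional chat group to moderate. No extra patients, visits or staff are needed, and the assigned programmes do not change. Separate groups will not stop patients from learning of the other arm by other means, which is why the exposure question is needed as well.

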### Relevant concomitant care permitted or prohibited during the trial {11d}

In order to make the patients receive the same rehabilitation as possible within 3 months after surgery, the early rehabilitation training is printed and taken home after discharge (Table 2). Participants will be informed that rehabilitation interventions, other than those that will be received during the period of the study, will not be allowed.

**Table 2 Tab2:** The early rehabilitation training

**Stage**	The early rehabilitation training
0–3 weeks	1. Using fascial knife to reduce swelling, 5 min 2. Moving patella, 2 series of 10 repetitions 3. Flexing knee joint (0–90°), three series of 10 repetitions 4. Straightening the knee joint to the level of the healthy side 5. Straight leg raising (SLR), three sets of 10 reps 6. Glute bridge, three sets of 10 reps 7. Walking with crutches
3–6 weeks	Besides the above scheme: 1. Increasing the flexion angle of the knee joint to achieve a full range of activities in 6 weeks 2. Gradually reducing the use of crutches, and do not use braces and crutches when walking for 6 weeks 3. The resistance can be increased when the straight leg is raised 4. Step up exercise 5. Intensive exercise of vastus medialis
6–12 weeks	If the above actions have been completed easily, go to the next step (pay attention to the training intensity in 8–10 weeks, and the ligament strength in the remodeling period is insufficient), and focus on flexibility training: 1. Squat training against the wall 2. Abduction training of muscles around the hip 3. Power bicycle training 4. Stair down training (after 10 weeks) 5. Seat squatting training

### Provisions for post-trial care {30}

If the patient’s function is limited due to participating in the test or due to the researcher’s manipulation problems, the center will provide follow-up rehabilitation treatment free of charge.

### Study outcomes {12}

#### Primary outcomes

Joint position sense: uses the isokinetic training instrument to evaluate the patient’s active position perception [13, 14]. The patient sits on the isokinetic training instrument, flexes the knee joint to 90°, and extends the knee 15, 45, and 75° actively, respectively. When reaching the target position, the patient stays for 10 s, puts it down, and rests for 10 s. The therapist sends a command to let the patient move to the target angle and maintain it for 10 s with the eyes closed. Record the difference between the angle and the angle when opening the eyes, and repeat it three times.Gait: ① We set up a 20-m straight line, open the Gait Watch 3D gait analysis system (JUMHO™, China), and calibrate its walking angle and other parameters at the starting point. Fix 7 sensors at the sacrum, outer femur, inner tibia, and dorsum of both feet of the subject, and try to stand at the starting point in a standard upright position. After calibration of the origin, the patient walks in a straight line for 20 m on a level ground in the designated non-interference ward; The hardware data collection system records the posture of the elderly during walking, calculates and saves motion data of the pelvis, hip, knee, and ankle joints in the three-dimensional plane, and synchronously transfers gait data to gait analysis software for analysis. Perform three-dimensional gait analysis and measurement on all subjects before and after the experiment, and collect spatiotemporal parameters such as gait speed, stride frequency, stride length, walking cycle, left and right stride length, dual support phase, left and right support phase, and left and right swing of the subjects, and repeat it three times. ② Locomotor rehabilitation index [15]: The walking speed was measured on a 20-m path. The participant walked at a comfortable pace (similar to how they normally walk in their daily lives). The participant began the test 3 m before the beginning position and was stopped 3 m after the arrival point, with the goal of disregarding positive and negative accelerations. Three times, with a three-minute break in between. Then calculate the average time of three times. Lower limb length was measured by great trochanter to the ground with a tape measure.$$\mathrm{Walking\ speed }= 20/\Delta \mathrm{t}$$where △t = time spent to walk through the entire walkway, in seconds.$$\mathrm{OWS\ }(\mathrm{optimal\ walking\ speed},\mathrm{ in\ m}/\mathrm{s}) =\mathrm{ sqrt }( 0.25 * 9.81 *\mathrm{ lower\ limb\ length\ }(\mathrm{or\ }0.54\ \mathrm{ of\ height}))$$$$\mathrm{LRI\ }(\mathrm{locomotor\ rehabilitation\ index},\mathrm{ in \%}) = 100 *\mathrm{ walking\ speed }/\mathrm{ OWS}$$Plantar pressure: The subject stands on the pressure plate normally(Kinvent™, France), with his feet naturally separated, and his upper limbs on both sides of his trunk. After the data is stable, the load ratio of the left and right front and rear feet is measured and repeated three times.

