### Trial design{8}

This trial is a single center, single-layer (the experimental group and the comparator group were randomly assigned in a 1:1 balanced manner), and the evaluator was blind.

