### Sample size {14}

Using the G Power 3.1.9.7 software, previous studies showed that between the proprioceptive training group and the comparator group, the effective amount of JPS joint position perception difference *d* = 0.97 [13]; According to power = 80%, alpha = 0.05, and *d* = 0.97, the required sample size *n* = 36 is calculated. Considering the loss of 10% sample size, 40 subjects are required.

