## Statistical methods

### Statistical methods for primary and secondary outcomes {20a}

The data are presented as the mean ± standard deviation for normally distributed continuous variables and as proportions for categorical variables. The continuous variables were compared using Student’s *t*-test, and categorical variables using *χ*^2^ test. To analyze the effectiveness of the trial with change over time (from baseline to week 6 and week 12), repeated measures analysis of covariance (ANCOVA) will be applied, and treatment, time, and the treatment × time interaction as independent variables. The results are reported as mean ± SD and their 95% CIs and *P* values < 0.05 were considered statistically significant.

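### Three outcome domains are primary under one general 0.05 threshold, but the stated 5% alpha and 80% power hold for a single joint-position comparison only

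*Protocol article*

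**What the plan says.** All references are to the Protocol article.

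- **Study outcomes {12}, Primary outcomes.** Three domains carry the primary label.
  - JPS: the participant "extends the knee 15, 45, and 75° actively, respectively", with three repeats. No summary across the angles is named.
  - Gait: the plan is to "collect spatiotemporal parameters such as gait speed, stride frequency, stride length, walking cycle, left and right stride length, dual support phase", followed by left and right support and swing. The variables are introduced as examples, so the list is open. A locomotor rehabilitation index is added.
  - Plantar pressure: load ratio of the left and right front and rear foot.
- **Statistical methods {20a}.** A repeated measures ANCOVA with treatment, time and their interaction covers change from baseline to weeks 6 and 12. The only threshold is that P "values < 0.05 were considered statistically significant". No lead endpoint, visit or order is given.
- **Sample size {14}.** The basis is "the effective amount of JPS joint position perception difference *d* = 0.97". It continues "According to power = 80%, alpha = 0.05", arriving at 36, and then "Considering the loss of 10% sample size, 40 subjects are required". Nothing is assumed for gait or plantar pressure.
- **Background and rationale {6a}** states the hypothesis in terms of gait and plantar pressure. **Objectives {7}** puts knee proprioception first and lower limb kinematics second.

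**The concern.** The document fixes three things that do not fit together: a wide primary set, one threshold for everything, and a sample size built on one member of the set. A reader of the final report would take 5% and 80% as properties of the trial's primary result. They are properties of one JPS comparison.

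Two consequences follow. First, a nominally significant result on any angle, gait variable or load ratio could be presented as a positive primary finding, and nobody could tell it from selection among many. Second, the domains that carry the stated hypothesis, gait and plantar pressure, have no power basis. A null result there would say little, and a positive one would have no stated error control.

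**Working it through.** **Inputs from the document.** d = 0.97, alpha 0.05 and power 80% (Sample size {14}); allocation "randomly assigned in a 1:1 balanced manner" (Trial design {8}); 10% loss; threshold 0.05 (Statistical methods {20a}). Sidedness is not stated.

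**Step 1. Reproduce the plan's figure.** For a two-sample t-test, two-sided alpha 0.05, power 80% and d = 0.97, the noncentral t solution is 17.70 per arm. This rounds up to 18, so 2 × 18 = 36, and 36 / 0.90 = 40. A one-sided test would give 28, so the plan evidently used a two-sided one. At 18 per arm the noncentrality is 0.97 × √(18/2) = 2.91 on 34 degrees of freedom, and power is 80.7%. The arithmetic is right for one comparison.

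**Step 2. Count the primary variables.**

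| Domain | Variables |
|---|---|
| JPS | 3 angles, or 1 if summarised |
| Gait | speed, stride frequency, stride length, cycle (4); left/right stride length (2); dual support (1); left/right support (2); left/right swing (2) = 11; plus the locomotor rehabilitation index = 12 (about 9 if left/right pairs are merged) |
| Plantar load | 1 to 4 |

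A moderate count is 1 + 12 + 1 = 14.

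**Step 3. Chance of at least one false positive.** If each of k tests is run at 0.05 and any one can be claimed, the rate for independent tests is 1 − 0.95^k. For one test per domain, 1 − 0.95³ = 0.143. For correlated tests, 200,000 draws of equicorrelated normal statistics were simulated. The correlations are assumed, since the document gives none.

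| Assumed correlation | 3 domains, one test each | 14 variables, one visit |
|---|---|---|
| 0.3 | 13.6% | 44% |
| 0.5 | 12.6% | 35% |
| 0.7 | 11.0% | 25% |
| 0.9 | 8.4% | 14% |

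Every entry exceeds 5%.

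**Step 4. Power for a single gait or plantar variable.** With 18 per arm and two-sided 0.05, 80% power requires d = 0.96. For assumed smaller effects, power is 65% at d = 0.8 and 31% at d = 0.5.

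**Step 5. What an alpha split would cost.** Bonferroni over three domains gives 0.05 / 3 = 0.0167. JPS power at 18 per arm falls to 65.3%. Restoring 80% takes 48 evaluable participants, and 48 / 0.90 = 53.3, so 54 enrolled. A single JPS primary endpoint, or a fixed sequence led by it, keeps 80.7%.

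**The case against.** **The rule is inferred.** The article gives a general significance threshold. It does not say that each primary variable is tested at 0.05, nor that any one success suffices. This stands, so the rates in Step 3 are conditional on that use. An adjustment or ordering could also sit in an analysis plan not shown, so its absence is not the fault. What the article itself fixes is three primary domains sized on one. A later alpha split would not resolve that, because the stated 80% would no longer hold at N = 40 (Step 5). Nor would requiring all three domains to succeed: false positives would be controlled, but even with independent tests and d = 0.97 in every domain, power would be 0.807³ = 0.53.

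**JPS looks like the lead endpoint.** It is listed first, is the first objective and is the only sized outcome. This stands in part: 5% and 80% are sound for one JPS comparison. But no angle, summary or visit is chosen even within JPS, and gait and plantar pressure carry the same primary label.

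**Larger error rates are tempting.** A reader might treat the 14 variables as independent (51%), or count both visits as separate tests (28 tests: 76% independent, 49% at correlation 0.5). The document supports neither. The gait variables are algebraically linked: cycle is the reciprocal of stride frequency, speed is stride length times frequency, and support and swing add up to the cycle. Both visits also enter one repeated measures model per variable, so 28 separate tests is not the stated analysis.

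**Conclusion.** The point holds in a limited form and should be settled before analysis. The stated alpha and power describe one JPS comparison, not the primary set as listed. If any primary success may be claimed at 0.05, the false-positive rate is about 14% for three independent domain-level tests and 12–13% at an assumed correlation of 0.5. For 14 variables at one visit it is roughly 35% at that correlation. Gait and plantar claims have no stated power, and 18 per arm is adequate only for effects near d = 0.96.

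A reader might go further and infer that the sample size is wrong. It is not: 36 and 40 reproduce exactly, and the fault is in their scope.

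The figures rest on assumed correlations, a two-sided t-test and 18 evaluable participants per arm.

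**What to change.** Before analysis:

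1. Name one JPS summary across the three angles, at one visit, as the sole primary endpoint at two-sided 0.05. Week 12 is one possibility, taken as a contrast from the planned repeated measures ANCOVA. N = 40 and about 81% power then stand, provided d = 0.97 is a fair assumption for the chosen summary and visit.
2. For gait and plantar pressure, choose one of two routes. Either test one pre-named gait variable and then one pre-named plantar variable in fixed sequence, each only if the preceding test is significant, or make both domains secondary with estimates and 95% CIs. Which variables, and in which order, is for the investigators to decide.
3. Label all remaining gait and plantar variables, the single angles and the other visit secondary or exploratory.
4. State under Sample size {14} that the power applies to JPS only.

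**Cost.** No extra participants are needed. The scientific cost is real: confirmatory claims on gait and plantar pressure, which carry the hypothesis in {6a}, become conditional on a JPS effect or supportive only. Administratively, the section on protocol amendments {25} sends major changes to the ethics committee and the registry. Trial status gives a recruitment start of 10 March 2023 (while also saying that recruitment has not begun), so the change should be dated and shown to precede any look at outcome data by arm.
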